## **6. TIME LINE AND PARTICIPANT FLOW**

### **6.1. Time Line**

The study will be conducted in six cohorts, each including 40 participants, over a 3-year period.

For the first cohort, recruitment will take place October 2016 – January 2017. The intervention, including weekly meetings, will take place between February and May 2017 for a total of 16 weeks. For the second cohort, recruitment will take place in December 2016 and January, 2017. The intervention, including weekly meetings, will take place between March and July 2017. Similar time frames will apply in the two subsequent years.

## **6.2. Participant Flow Based on Power Analysis**

In order to accommodate this number of participants, baseline metabolic assessments will occur as follows for the first cohort:

January 6: 2 participants  
January 9-13: 10 participants  
January 17-20: 8 participants  
January 23-27: 10 participants  
January 30-Feb 3: 10 participants

The MR spectroscopy studies will be limited to 40 participants (20 per study arm) total. These evaluations will be scheduled during the above scheduled days.

The Diet Group sessions for the first cohort will be held for 16 weeks, from February 1 through May 17, 2017.

For the first cohort in 2017, the 16-week metabolic assessments will occur as follows:

May 18-19: 4 participants  
May 22-26: 10 participants  
May 30-June 2: 8 participants  
June 5-9: 10 participants  
June 12-15: 8 participants

For the second cohort, the assessment and intervention dates will be approximately one month later than those for the first cohort.

## **7. PROTECTION OF HUMAN RESEARCH PARTICIPANTS**

### **7.1. Risks to the Subjects**

**Sources of Materials:** Participants will be asked to complete questionnaires, provide blood samples, and have several physical assessments.

**Human Subjects Involvement and Characteristics:** The proposed research will include participants at least 18 years of age.

**Potential Risks:** Participation in the study entails the following risks:

1. Blood draws can cause transient pain, occasionally cause bruising, and may cause bleeding.
2. A well-planned vegan diet provides all the nutrients people need except for vitamin B12. People with a vitamin B12 deficiency may suffer from anemia and neurologic damage.
3. Loss of confidential information.

## **7.2. Adequacy of Protection against Risks**

**Recruitment and Informed Consent:** Participants will be informed of the study's goals and procedures and review the inclusion and exclusion criteria. Volunteers who appear to meet the criteria for participation will be invited to a group or individual interview with the principal investigator and the study coordinator, who will explain the study in detail, answer questions, and provide a written consent form, as approved by the IRB. Participants will have the opportunity to ask any questions individually in a private setting and may take as much time as they would like to review the informed consent document. The consent form will be signed by the volunteer participant and study coordinator. The principal investigator will certify that the research study has been explained to the volunteer, including the purpose, procedures, possible risks, and potential benefits associated with participation and that any questions have been answered to the volunteer's satisfaction.

Participants' personal physicians will be notified of their involvement in the study and that the investigators will not manage any aspects of their medical care.

To maintain confidentiality, all laboratory specimens, questionnaires, forms, and data sheets will identify participants by their assigned numbers only. Data and safety monitoring are described below.

**Phlebotomy risks.** All blood draws will be carried out by an experienced registered nurse, employed by PCRM. .

**Vitamin B12 deficiency.** All Diet Group participants will be given a supply of vitamin B12, 100 micrograms, and will be asked to take it daily. Participants will also be counseled to continue B12 supplementation if they plan to continue following a vegan diet.

**Loss of confidential information.** We will make every effort to keep all research records private to the extent allowed by law. We will use an identification number on forms, instead of identifiable information. All study documents will be kept in locked filing cabinets and in password protected electronic files at PCRM's office. Information we

learn from this study may be shared at scientific or medical meetings and may be published, but participants will not be personally identified.

Our protocol also includes the following safeguards:

1. All participants will remain under the care of their personal healthcare providers.
2. All participants will continue on the medications they were using at study entry, unless modified by their personal physician(s).

We therefore believe that the risks to participants in a dietary intervention trial are minimal, while the scientific and public health merit of such an investigation is high. By studying the benefits of a dietary intervention, we hope to obtain valuable research data.

**Confidentiality.** To maintain confidentiality, all laboratory specimens, questionnaires, forms, and data sheets will identify participants by their assigned numbers only. Data and safety monitoring are described below.

### **7.3. Potential Benefits of the Proposed Research to the Participants and Others**

Given that, over the long run, excess body weight contributes to morbidity and mortality, the dietary instruction and consistent support provided may be of substantial benefits for the Diet Group. The Control Group will be given detailed information on how to follow the intervention diet at the study's conclusion.

### **7.4. Importance of the Knowledge to Be Gained**

Weight problems are extremely common, and gaps remain in our understanding of how intervention diets work. This study is founded on clear theoretical constructs and compelling previous data on both the efficacy and acceptability of the experimental intervention, as well as preliminary findings on its mechanisms of action. It investigates what may be a major advance in the understanding of the role of diet in weight control. The risks to participants are small, and the potential benefits are significant.

### **7.5. Assessment and Reporting of Adverse Events**

An adverse event is any adverse physical or clinical change experienced by a participant. This includes the onset of new symptoms and the exacerbation of pre-existing conditions. In order to avoid bias in eliciting reports of adverse events, participants will be asked, during assessments at the end of each study period, "Have you had any new symptoms, injuries, illness or side effects or worsening of pre-existing conditions?" at each visit.

All adverse events will be recorded in the participant's record and on the IRB continuing review form. The severity of the adverse event will be assessed, and actions/outcomes (e.g., hospitalization, discontinuation of therapy, etc.) will also be recorded.

Any actions taken and follow-up results will also be recorded on the appropriate page of the IRB continuing review form, as well as in the participant's record. Follow-up laboratory results will be filed with the participant's record. All adverse events occurring at a site will be reported by the investigator to the IRB according to the Data and Safety Monitoring Plan, described below.

The following definitions will be used:

|                    |                                                                                                                             |
|--------------------|-----------------------------------------------------------------------------------------------------------------------------|
| Minimally serious: | Awareness of sign, symptom, or event, but easily tolerated.                                                                 |
| Somewhat Serious:  | Discomfort enough to cause interference with usual activity and may warrant investigation.                                  |
| Very Serious:      | Incapacitating, with inability to do usual activities, or significantly affects clinical status, and warrants intervention. |
| Life-threatening:  | Immediate risk of death.                                                                                                    |

The research team will also assess the relationship of any adverse event to the study intervention, based on available information, using the following guidelines:

|                 |                                                                                                                                      |
|-----------------|--------------------------------------------------------------------------------------------------------------------------------------|
| 0 =
Unlikely | No temporal association, or the cause of the event has been identified, or the study interventions cannot be implicated.             |
| 1 =
Possibly | Temporal association, but other etiologies are likely the cause; however, involvement of the study interventions cannot be excluded. |
| 2 =
Probably | Temporal association or other etiologies are possible, but unlikely.                                                                 |

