screening process, prospective volunteers will be provided the study coordinator's phone number and contact information in order to be able to reschedule and cancel their appointments, if necessary.

Prospective volunteers will then be asked to complete a practice 2-day dietary record to demonstrate their ability to track nutrient intake for research purposes. A letter will be sent to the participants to remind them to complete their 2-day diet record with instructions (**Appendix 6**). When completed, these records will be reviewed for completeness by a registered dietitian.

Volunteers who have completed the informed consent process and practice dietary records and meet the study participation criteria will be asked to schedule individual appointments for baseline assessments. There, they will be asked to fill out new 3-day dietary records. Volunteers can either submit questionnaires online, print, scan and email them, or send them through regular mail. Those who satisfactorily complete the baseline assessments and 3-day dietary records will be enrolled in the study.

The cost of all tests and procedures will be covered by PCRM. If any examination or test reveals that a participant has a medical condition that requires additional diagnostic tests or treatment, research staff will advise the participant of that fact, but will not provide such additional diagnostic tests or treatment. There is no cost for the weekly group sessions. Parking will be free during participants' visits to the PCRM office for assessments, meetings, and group sessions.

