#### **4.2. Dietary Instruction and Group Meetings**

Diet Group participants will be asked to attend weekly, one-hour group sessions for support and education. (**Class Curriculum, Appendix 8**). No weekly support or education will be provided to the participants in the Control Group.

All group sessions will be conducted by a registered dietitian, nurse, physician, cooking instructor, or research staff and will include information on nutrition, meal planning, shopping, food preparation techniques, recipes, and everyday dietary challenges, such as dining out and healthful snacking. The classes will also include education on topics such as maintaining a healthy weight, cholesterol, hypertension, diabetes, and other health issues.

For some sessions, participants will be encouraged to bring a spouse, partner, family member, or friend. To facilitate interaction between diet instructors and participants, classes will be conducted in sections of approximately 15 participants.

The curriculum is based on the investigators' prior studies and uses concepts from the Health Belief Model developed by researchers with the Public Health Service and adapted by others. This model describes constructs that predict health-related behaviors and should be considered when planning behavioral change strategies. These include perceived susceptibility, severity, benefits, and barriers, as well as cues to action, and self-efficacy. Our participants are already aware that they are overweight and may benefit from diet changes. Nonetheless, they need help in overcoming barriers

and gaining confidence in their ability to implement new dietary habits. We have therefore focused the content of the weekly support group sessions on integrating practical skills (e.g., menu planning, food preparation, dining out, healthful snacking) with their growing understanding of how dietary choices affect health. In order to facilitate individual experience with the prescribed diet, practical skills are presented early, while intellectual understanding of more complex health issues (e.g., how diet affects heart disease risk) is presented later. Each group session includes time for participants to discuss their successes and challenges, and group problem-solving is encouraged.

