### **7.8. Data and Safety Monitoring Plan**

Data and Safety Monitoring functions will be performed by the principal investigator (PI, [name].), study coordinators ([name], [name], and [name]), study statistician, and a Safety Officer who is a physician who is not part of the research staff and has no role in care of the participants. The Safety Officer will have no scientific, financial, or other conflict of interest related to the trial.

Prior to the study onset, the study statistician and Safety Officer will review the research protocol, informed consent documents, and plans for data and safety monitoring.

During the recruitment phase, the study coordinator and PI will review enrollment weekly. At monthly intervals, they will produce a report describing the study's progress, including accrual, demographics, thoroughness of baseline data, subject status (reporting concurrent illnesses, withdrawal of consent, or loss to follow-up), and adherence to participation criteria, informed consent procedures, and the study protocol. The reports will be submitted to the study statistician and Safety Officer.

Prior to participant randomization, a full history of each participant's pre-existing symptoms and medical problems will be recorded. During each monitoring visit, study participants will be asked if any medical symptom, problem, or event has occurred or if there has been any change in pre-existing symptoms.

All serious events (hospitalization, serious illness, or disability) will be recorded and reported to the PI and Safety Officer. The PI will notify the IRB within 24 hours of recognition of the event by study personnel. All non-serious events will be reported and reviewed by the PI within one week. Study personnel will inform the primary care physician of all events occurring in his/her patients within 48 hours of recognition of the event.

At monthly intervals, the study coordinator and PI will prepare and submit to the study statistician and Safety Officer a report covering each of the following areas: (1) performance (including adherence to the study protocol and maintenance of data integrity and confidentiality), (2) safety (including abnormal laboratory values, adverse events, serious adverse events, deaths, and disease- or treatment-specific events), and (3) treatment effects, including medication changes.

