The study statistician and Safety Officer will review each safety report within one week of receipt. The study statistician will review these reports to assess whether event rates are of statistical concern and, if so, will alert the Safety Officer, the PI, and the IRB. The study statistician and Safety Officer will also consider factors external to the study, e.g., new scientific developments, that may affect the safety of participants or the conduct of the trial.

The Safety Officer will make recommendations as necessary to the PI. If the Safety Officer recommends a study change for patient safety or for ethical reasons, or if the study is closed early due to slow accrual, the PI will be responsible for implementing the recommendations as expeditiously as possible. If the PI does not concur with any recommendation of the Safety Officer, both will be responsible for reaching a mutually acceptable decision.

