## **7.9. Stopping Rules**

At the conclusion of the 16-week intervention period for the first cohort, the study statistician will prepare a report on clinical changes and adverse events for presentation to the PI and the Safety Officer. If evidence available at that point clearly shows either (1) an effect of the intervention diet on postprandial metabolism or (2) harm associated with the intervention diet, the Safety Officer may recommend early termination of the study.

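### Adverse-event questioning is timed in three inconsistent ways; with weekly contact in the Diet Group only, non-serious event rates are open to unequal ascertainment between arms

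*Protocol*

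**What the plan says.** Section 7.5 introduces one standard question about new symptoms, injuries, illness, side effects or worsening conditions: "In order to avoid bias in eliciting reports of adverse events, participants will be asked, during assessments at the end of each study period". After the wording of the question, the sentence closes by saying it is put at each visit. The section also says that all adverse events go into the participant's record.

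Section 7.8 gives another timing: "During each monitoring visit, study participants will be asked if any medical symptom, problem, or event has occurred". No section defines or schedules a monitoring visit. Table 1 lists clinical status and symptoms at weeks 0 and 16 only, for both groups alike.

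On contact, section 4.2 gives the Diet Group weekly one-hour sessions and says of the other arm: "No weekly support or education will be provided to the participants in the Control Group". In a sentence about parking, section 3.3 speaks of "visits to the PCRM office for assessments, meetings, and group sessions".

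On use of the data, section 7.8 requires monthly reports that include adverse events, and adds: "The study statistician will review these reports to assess whether event rates are of statistical concern". Section 7.9 provides for a report after the first cohort's intervention period. On clear evidence of "harm associated with the intervention diet, the Safety Officer may recommend early termination of the study".

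**The concern.** The question is introduced as a safeguard against bias in eliciting events. That safeguard works only if both arms have the same opportunity to report. Here one arm meets staff every week and the other may not be seen for 16 weeks, and the text does not settle whether the question is asked at those weekly meetings.

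Minor events are the kind most easily forgotten over 16 weeks and most easily mentioned at a weekly meeting. With equal true rates, the diet could appear to cause more of them. The statistician reviewing monthly rates would have no matching control rate for participants still in follow-up, and the same data feed a judgement on harm after only 40 participants. An apparent excess, or the lack of one, would be hard to interpret.

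**Working it through.** **Step 1: the timings side by side.**

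| Place | When events are asked about |
|---|---|
| Section 7.5, start of sentence | Assessments at the end of a study period |
| Section 7.5, end of same sentence | Each visit |
| Section 7.8 | Each monitoring visit (undefined) |
| Table 1 | Weeks 0 and 16, both groups |

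The first and last agree. The second agrees with them only if a visit means a scheduled assessment. The third cannot be placed.

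**Step 2: scheduled in-person contacts after baseline.** Section 6.2 holds the first cohort's sessions for 16 weeks, 1 February to 17 May 2017, which is 16 weekly dates.

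- Diet Group: 16 sessions + 1 week-16 assessment = 17. Dietary recalls at weeks 3 and 8 (section 4.4) and calls after missed meetings (section 4.5) come on top.
- Control Group: 1, the week-16 assessment. Section 3.6 says week-8 weight will be analysed, but Table 1 has no week 8 and no control visit then is stated. If there is one, the count is 2.

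**Step 3: consequence under each reading.**

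- *Sessions are visits.* The question is put up to 17 times in the Diet Group and once (perhaps twice) in controls. Solicited events are unequally ascertained.
- *End-of-period assessments only.* The question is put once after baseline in each arm, so solicited events are equal. Events mentioned at weekly sessions still enter the record under section 7.5, and controls have no comparable occasion. Only volunteered events are unequal.

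On both readings, non-serious events arising between weeks 0 and 16 reach staff during that interval almost only from the Diet Group.

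**Step 4: illustrative size, first reading only.** The protocol states no event rate, recall rate or harm threshold, so there is no plan figure to reproduce. With equal true risk q and capture probabilities c(D) and c(C), the apparent risk ratio is q·c(D) / q·c(C) = c(D)/c(C). All capture values are assumptions.

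- c(D) = 0.9: 0.9/0.8 = 1.13; 0.9/0.6 = 1.5; 0.9/0.4 = 2.25.
- c(D) = 1: 1/0.7 = 1.4; 1/0.3 = 3.3.
- c(D) = c(C): 1.0.

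If someone tested the difference at two-sided 0.05, with c(D) = 0.9, c(C) = 0.6 and q between 0.3 and 0.5, the chance of a spurious significant excess on the diet would be about 10–16% with 20 per arm (a 40-person cohort split equally, also assumed). It would be 28–51% with the 81 per group of section 5.1. The nominal value in that direction is 2.5%.

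**Step 5: timing of the first-cohort report.** Sessions end on 17 May; week-16 assessments run from 18 May to 15 June (section 6.2). A report prepared strictly when the intervention ends could contain little or no solicited control data. Since it must also judge postprandial metabolism measured at week 16, it presumably waits, but section 7.9 does not say so.

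**The case against.** A reader might infer that the plan asks the Diet Group 17 times and controls once, so that the harm comparison is biased. The documents do not support that as settled. The opening of the section 7.5 sentence limits the question to end-of-period assessments, and Table 1 agrees, without distinguishing the arms. The use of the word visits for group sessions comes from a sentence about parking, not a rule for safety collection. The sections describing the sessions mention no adverse-event questioning. On that reading the solicited question is equal, and this part of the objection stands.

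A reader might also infer a formal between-arm harm test. None is named. Section 7.8 asks the statistician for a judgement on event rates, section 7.9 leaves a recommendation to the Safety Officer, and section 7.5 assesses each event's relation to the intervention individually. This also stands.

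Two further points have weight. Serious events are reported within 24 hours of becoming known, whatever the visit schedule (section 7.6), so they are less exposed, though becoming known itself depends partly on contact. Any distortion would probably make the diet look worse, and it does not touch the primary outcomes.

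The objection does not remove the conflict of timings, the undefined monitoring visit, or the lack of any stated interim source of non-serious control events for reports in which event rates are to be judged. Nor can this be left to an analysis plan: when and from whom events are collected is a rule of conduct, and control events never asked about cannot be recovered later.

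**Conclusion.** The point holds as an exposure to bias, not as demonstrated bias. The three timings in sections 7.5 and 7.8 do not agree with one another or all fit Table 1. The firm figure is the contact count: 17 scheduled in-person contacts after baseline against one clearly scheduled (two if a control week-8 weighing exists). The likely direction is more recorded non-serious events on the diet. The extent depends on which reading staff follow and on how well controls recall 16 weeks; the ratios and false-signal probabilities are illustrations on assumed values and apply only if the question is asked at sessions. The matter should be corrected because these data enter the monthly rate review and can support a recommendation to end the trial early.

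**What to change.** 1. Reconcile sections 7.5 and 7.8 with Table 1: replace the references to each visit with named time points, and define the monitoring visit or delete it.
2. State that any between-arm adverse-event comparison, and the comparative non-serious harm evidence considered under section 7.9, rest on the same scripted question at the week-16 assessment in both arms, plus serious events from any source. Say that the first-cohort report follows that cohort's last week-16 assessment.
3. List events volunteered at Diet Group sessions separately, outside the comparison.
4. Label non-serious rates in the monthly reports as non-comparative.

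This changes wording only, adds no visits, and leaves the review of individual events and the Safety Officer's discretion as they are. The cost is that minor events with poor recall are under-counted equally in both arms in the comparative table; those raised at sessions still appear in the separate listing. It does not create an interim control rate. If one is wanted, the alternative is to put the same question to both arms on the same schedule, for example by telephone for controls, at the price of extra staff contact.

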**Table 1: Study Procedures Schedule**

| Week                                          | 0 | 16 |
|-----------------------------------------------|---|----|
| 3-day diet record                             | √ | √  |
| International Physical Activity Questionnaire | √ | √  |
| Clinical status and symptoms                  | √ | √  |
| Medication use                                | √ | √  |
| Height                                        | √ |    |
| Body weight*                                  | √ | √  |
| Comprehensive Metabolic Panel (CMP)           | √ |    |
| Plasma lipids and lipoproteins                | √ | √  |
| A1c                                           | √ | √  |
| Glucose tolerance testing                     | √ | √  |
| REE                                           | √ | √  |
| Postprandial metabolism (TEF)                 | √ | √  |
| Body composition                              | √ | √  |
| IMCL and hepatic lipid (pilot)                | √ | √  |
| Microbiome analysis (uBiome)                  | √ | √  |
| Endothelial function (EndoPAT)                | √ | √  |

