#### **4.5. Participant Retention**

Participants' interests for volunteering will be ascertained during screening. Those with reasons for volunteering other than a desire to improve their health or to advance scientific understanding may be rejected. The exclusion criteria also eliminate individuals with a history of unresolved substance abuse, which may influence retention.

Participants will be instructed that attendance at meetings is essential to study participation. The research team will take attendance at each meeting. The research staff will make phone calls to participants who do not attend.

In the weekly meetings, group support will be facilitated through group discussions and encouragement to share successes and difficulties with the prescribed diet. Meeting content will remain varied, including nutrition lectures, health education, cooking demonstrations, and opportunities to taste food. Family members will be invited to certain support group sessions. A voluntary listserv will allow Diet Group members to exchange information, recipes and ideas between meetings. Only participants, study coordinators, and the PI will be allowed to post on the list serve and the content of the list serve will be accessible only by them.

Participants who complete all assessments at weeks 0 and 16 will be paid \$100 at completion of their final assessments.

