### **5. STATISTICAL PROCEDURES**

#### **5.1. Power Analysis**

##### **Power Analysis for Overall Study**

Sample size will be based on the change in postprandial metabolism (thermic effect of food) previously observed with a plant-based diet, compared with an active dietary control. The current power analysis assumes there will be a single t-test for the comparison of the changes in thermic effect of food observed in the two study groups, with an alpha level of 0.05.

In the prior study, the change at 14 weeks for the thermal effect of food was 4.7 with an SD of 12 in the intervention arm, and 0.3 with an SD of 9.4 in the control arm. Assuming that the true treatment effect is 4.4 kcal/170 min and that the SD of the change will be 12.0 units in the Diet Group and 9.4 units in the Control Group, as previously observed, the sample size required is 96 per arm (192 total) for 80% power, 109 per arm for 85% power, 128 per arm for 90% power.

However, if this magnitude of treatment effect is assumed to be present at the same magnitude of effect at each of the 5 evaluation points used in TEF assessment and assuming that the standard deviation is about 10.85 points for all observations, with 5 observations per participant, correlated at a magnitude of 0.7 with each other, the sample size required is 73 participants per arm (146 total) with 80% power, 83 per arm with 85% power, 98 per arm for 90% power.

Assuming an attrition of 10%, the required sample size is 81 per group, or 162 total for 80% power.

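### The adverse-event question depends on attending a visit, and nothing provides for asking participants in either arm who leave early, so non-serious events around withdrawal can be missed

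*Protocol*

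**What the plan says.** Section 7.5 gives one standard question, intended to elicit adverse events without bias. It gives the timing twice in one sentence: "participants will be asked, during assessments at the end of each study period", and then, after the question itself, "illness or side effects or worsening of pre-existing conditions?' at each visit". Section 7.8 states: "During each monitoring visit, study participants will be asked if any medical symptom, problem, or event has occurred". The Protocol does not define a monitoring visit. In Table 1 the row "Clinical status and symptoms" is ticked at weeks 0 and 16 and at no other time, and no early-termination visit is listed.

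Contact between these two points differs by arm. Section 4.2 says "Diet Group participants will be asked to attend weekly, one-hour group sessions for support and education", and then "No weekly support or education will be provided to the participants in the Control Group". Section 4.5, on retention, adds: "The research staff will make phone calls to participants who do not attend". It does not say what is asked in those calls.

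On dropout, section 5.1 states: "Assuming an attrition of 10%, the required sample size is 81 per group, or 162 total for 80% power". Section 5.4 compares dropout rates between groups by chi-square and does not mention the reason for leaving.

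**The concern.** Under each of the three descriptions of timing, the question reaches a participant only if he or she attends something. A participant who feels unwell and stops coming has no scheduled occasion on which to be asked, in either arm. People who leave early are a group in which tolerability problems may be concentrated, so the section that aims to avoid bias in eliciting events has a gap where bias is plausible.

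The Protocol does provide for dropouts on the efficacy side: section 5.3 carries earlier values forward and returns body weight to baseline. It has no matching provision for safety data. The records affected are those behind the monthly safety reports (7.8) and the report after the first cohort, on which the Safety Officer may recommend stopping for harm (7.9).

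**Working it through.** **Plan's own figure.** The only stated number that bears on this point is attrition. From 73 per arm (section 5.1), 73 / (1 − 0.10) = 81.1. The Protocol states 81; strict rounding up gives 82, a difference that does not matter here. Expected leavers per arm: 0.10 × 81 = 8.1, taken as 8, which leaves 73 completers.

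**Is there any route to a leaver's non-serious event?**

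| Provision | What it covers | Does it put the question to a leaver? |
|---|---|---|
| 7.5, standard question | End-of-period assessments and visits | Only if the person attends |
| 7.8, monitoring visits | Undefined visits | Only if the person attends |
| Table 1 | Weeks 0 and 16 | No early-termination visit |
| 4.2, weekly sessions | Diet Group, for support and education | No adverse-event question stated; a leaver stops attending |
| 4.5, calls to non-attenders | Missed meetings; Control has no weekly sessions to miss | Content not stated |
| 7.5, discontinuation as an outcome | An event already recorded | Records; does not elicit |
| 7.6, serious events | Serious events that become known, up to the last visit | Not for non-serious events |
| 7.8, withdrawal and loss to follow-up | Monthly report described for the recruitment phase | Counts status; does not ask about symptoms |

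Several of these could bring an event to light by chance. None requires that the question be asked.

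**Scale, with all randomized participants as denominator.** The Protocol gives no adverse-event rate and no reasons for dropout, so the following is an assumption shown as a range. Let *f* be the share of the 8 leavers who had an event, and suppose none is captured. The shortfall in the arm's rate is 8 × *f* / 81, whatever the rate among completers:

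- *f* = 0%: 0 / 81 = 0 points
- *f* = 25%: 2 / 81 = 2.5 points
- *f* = 50%: 4 / 81 = 4.9 points
- *f* = 100%: 8 / 81 = 9.9 points

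**Scale, with completers as denominator.** If completers have rate *c*, the error is 8 × (*f* − *c*) / 81. With *c* = 50% and *f* = 0% it is 8 × (−0.5) / 81 = −4.9 points (recorded rate too high). With *c* = 10% and *f* = 100% it is 8 × 0.9 / 81 = 8.9 points (recorded rate too low). On this denominator the sign is not fixed.

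**Between arms.** Suppose both arms have a true rate of 30%, which is 24.3 events in 81. If from none to all 8 Diet leavers had an event that is lost, the Diet Group shows between 30% and (24.3 − 8) / 81 = 20.1%. If Control participants, without weekly contact, recall 50% to 100% of their events at week 16 (assumed), Control shows 15% to 30%. The ranges overlap, so the recorded difference could run either way.

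**First-cohort look (7.9).** Section 6.1 puts 40 participants in a cohort. With equal allocation (assumed) that is 20 per arm and, at 10%, about 2 leavers per arm. Each missed event is then 1 / 20 = 5 points of that arm's rate.

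**The case against.** A reader might infer that leavers are never asked, that the safety data describe completers only, and that Diet Group harm is therefore understated. The strongest reply is that the Protocol shows none of these.

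The sentence in 7.5 does not stop at end-of-period assessments; it goes on to each visit, and 7.8 adds monitoring visits. Whether weekly sessions count as visits is left open. Section 7.5 has all adverse events recorded, 7.8 has non-serious events reviewed within a week and reported monthly, and 7.6 covers serious events whenever they become known. The Diet Group is seen weekly and non-attenders are telephoned, so a Diet participant who becomes unwell has several chances to say so. A Control participant has far fewer, and Control leavers fall into the same gap. Finally, tabulating withdrawals by reason is commonly left to a statistical analysis plan, which is not at hand.

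Most of this stands. It rules out a claim that leavers are never asked, a claim that only completers are counted, and any claim about the direction of the difference between arms. What it does not supply is a rule that the question be put to someone who leaves. The calls in 4.5 concern attendance, recording discontinuation presupposes a known event, and the serious-event route does not reach ordinary symptoms. How events are elicited is fixed in the Protocol itself, so an analysis plan could not repair it afterwards.

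**Conclusion.** The gap is real and limited. Sections 7.5 and 7.8 and Table 1 differ on when participants are asked, all make the question conditional on attendance, and none provides for early leavers in either arm. Non-serious events around withdrawal can be lost among the expected 10%. Over all randomized participants, an arm's recorded rate can then be too low by 0 to 9.9 points, or by 2.5 to 4.9 points if a quarter to a half of leavers had an event. These sizes assume 8 leavers of 81 and no capture by any other route; the Protocol supplies no event rate to narrow them.

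The conclusion that the Diet arm's harm is understated relative to Control does not follow. It would need events to drive dropout mainly in the Diet Group and to escape the weekly contact there, and the Protocol gives no data on either. The net bias between arms is unknown. This is a cheap improvement to safety ascertainment; it does not show that the safety comparison is wrong.

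**What to change.** In section 7.5, add that the same standard question, together with the reason for leaving, is put to every participant in either arm at the time of leaving, by telephone if needed. Anyone without a week-16 visit who was not reached at exit is asked by the week-16 date. Participants who withdraw consent to contact are exempt. The answers go into the adverse-event record, and withdrawals for an adverse event are reported by arm alongside the dropout comparison in 5.4. In the same edit, state which contacts count as visits in 7.5 and monitoring visits in 7.8, and align Table 1 with them.

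Cost: about 0.10 × 162 = 16 calls for the powered sample, or 0.10 × 240 = 24 for the six cohorts of 40 in section 6.1, made by staff who already telephone non-attenders. The downsides are some self-report by telephone, recall over up to 16 weeks when the exit contact is missed, and some leavers who cannot be reached. Because the rule is the same in both arms, it does not depend on which way the bias runs.
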